#### Analyses for aim one

To characterize the quality of implementation we will carry out a series of descriptive analyses and examine level of fidelity in four domains (described above). Implementation in intervention schools and in waitlist control schools (during the implementation phase) will be examined. It is possible that implementation in waitlist control schools will be of higher quality since this will be the second opportunity for implementation after a year of experiences, supervision and support. We will examine the two groups separately first, and then combine if no meaningful differences are found.

#### Analyses for aim two

To evaluate impact on teacher practices, we will apply linear mixed-effect models (apply SAS PROC MIXED procedure [68]) that will adjust for school nesting [69]. We will model post-intervention teacher practices (time two (immediate post intervention or six months after baseline) as a function of intervention, adjusting for time one teacher practices. To evaluate whether teacher practices are maintained over time (time three, seven months after post intervention or the first term of new school year), similar mixed-effect models will be applied. However, only the intervention sample will be analyzed (given that the waitlist control teachers will have received the intervention by time three). We will use repeated data over time (times two and three). We will model teacher practices post-intervention as a linear function of time, adjusting for baseline practices. In addition to random intercepts and slopes for individual teachers, the model will include random effects for schools. If the time effect is not significant, this will indicate maintenance of impact.

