**Methods/Design:**

The design of this study is guided by two implementation frameworks, the Consolidated Framework for Implementation Research and the Teacher Training Implementation Model, that consider multidimensional aspects of intervention fidelity and contextual predictors that may influence implementation and teacher outcomes. Using a cluster randomized design, 10 schools in Uganda will be randomized to either the intervention group (five schools) or the waitlist control group (five schools). A total of 80 to 100 early childhood teachers will be enrolled in the study. Teacher utilization of evidence-based strategies and practices will be assessed at baseline, immediate post-intervention (six months after baseline), and at seven months post-intervention (during a new academic year). Fidelity measures will be assessed throughout the program implementation period (during professional development and consultation sessions). Individual teacher and contextual factors will be assessed at baseline. Data will be collected from multiple sources. Linear mixed-effect modeling, adjusting for school nesting, will be applied to address study questions.

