## Methods/Design

### Design

This study applies a matched-pair cluster randomized waitlist controlled design. To ensure approximately similar characteristics in the intervention and control conditions, a statistician unfamiliar with the study schools will match the schools based on size (number of teachers and students). Five pairs of schools will be identified. Schools will be selected from a previous study of children’s health ([name] and [name] unpublished observations), which randomly selected 30 schools from the schools registered under Ministry of Education in Kampala, Uganda. The 10 schools for the RCT will be selected from this pool of 30 schools because they all indicated interest in participation. Within each pair, one school will be randomly assigned to intervention, and the other to the waitlist control condition (receiving intervention after the RCT post-assessment). By the follow-up assessment in intervention schools, all 10 schools will have received intervention. The study has been approved by Institutional Review Boards (IRB) of New York University Langone Medical Center (IRB number: S13-00362), Makerere University (IRB number: SBS110), and Ugandan National Science and Technology (IRB number: SS3194).

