### Sample size and power

We conducted power analyses for teacher outcomes (the primary evaluation outcomes), assuming intention-to-treat analyses will be applied. Power analysis for aim three (contextual moderators) is not computed given the exploratory nature and lack of empirical evidence in this area of research. In cluster match-pair randomized designs, in addition to the usual study design parameters, the effect sizes detectable with 80% power of two-sided tests with level of significance α = 0.05 depend on the cluster (school) sizes (m), the intra-class correlation (ICC) associated with the cluster and the correlation between the schools within a pair (ρ). In technical terms, the clustering leads to a decrease of the actual sample size (N) by a factor called variance inflation factor (VIF = 1 + (m-1) ICC). The effective sample size (N*) in the case of cluster randomization is N* = N/VIF. Akin to a paired t-test, randomization within matched pairs can increase the power of a test, especially if ρ is large. Depending on the analytic model, the magnitude of the detectable effects can also be varied. For example, a model which includes covariates that account for some variance in the outcome, such as baseline levels of the outcome, would be more powerful (and would provide adequate power to detect smaller effects) than a model that does not make use of covariates [57].

We estimate the magnitude of the effects that are detectable with 10 schools, matched in five pairs, and 80 to 100 teachers (or eight to 10 teachers per school) with respect to post-intervention outcomes, at 80% power of a 2-sided test with level of significance α = 0.05. The following assumptions are made in those computations: 1) the baseline values of the outcome and other baseline covariates in the model account for 20 to 50% of variance of the post-intervention outcomes (estimated variance obtained from trials conducted in the United States); 2) correlations of the outcome measures between schools within a pair (ρ) will be high, ranging from 0.50 to 0.70; and 3) ICCs associated with clustering of teachers within a school will range from 0 to 0.10. The detectable effects (Cohen’s d) would be d = 0.11 to 0.29. The proposed study will have sufficient power to detect impact on teacher outcomes that are meaningful and realistic.

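### The stated detectable effect takes credit for matched pairs, but the stated time-two model has no pair term, so the two describe different tests

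*Protocol article*

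**What the plan says.** - **Design.** The article states "This study applies a matched-pair cluster randomized waitlist controlled design". A statistician will "match the schools based on size (number of teachers and students"), "Five pairs of schools will be identified", and "Within each pair, one school will be randomly assigned to intervention, and the other to the waitlist control condition".
- **Sample size and power.** The calculation is for "10 schools, matched in five pairs, and 80 to 100 teachers (or eight to 10 teachers per school"), at 80% power and two-sided α = 0.05. It lists the correlation between paired schools (ρ) among the quantities that set the detectable effect and adds: "Akin to a paired t-test, randomization within matched pairs can increase the power of a test". The assumptions are ρ = 0.50 to 0.70, ICC = 0 to 0.10, and covariates explaining 20 to 50% of the outcome variance. The result is d = 0.11 to 0.29.
- **Analyses for aim two.** "we will apply linear mixed-effect models (apply SAS PROC MIXED procedure [68]) that will adjust for school nesting [69"]. Time-two practice is modelled on intervention, adjusting for time-one practice. The Abstract agrees: "Linear mixed-effect modeling, adjusting for school nesting, will be applied to address study questions". Pair is not named anywhere under Statistical methods, as a fixed or a random effect.

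**The concern.** In a pair-matched cluster trial, ρ reduces the standard error of the intervention effect only if the analysis removes the between-pair variation. A model with a school effect and no pair leaves that variation in the error term. The article therefore claims a gain in its power section that the model it describes cannot deliver.

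At stake is whether ten schools can answer the aim-two question. The article concludes that power is sufficient for meaningful and realistic effects, and that conclusion rests on the 0.11 to 0.29 range. If the range belongs to a different test, a null result could be read as evidence against effects that the trial was never able to detect.

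**Working it through.** **Inputs** (Sample size and power): 10 schools; N = 80 to 100 teachers, so m = 8 to 10 per school; R² = 0.20 to 0.50; ρ = 0.50 to 0.70; ICC = 0 to 0.10; 80% power; two-sided α = 0.05.

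Best case: N = 100, R² = 0.5, ρ = 0.7, ICC = 0. Worst case: N = 80, R² = 0.2, ρ = 0.5, ICC = 0.10. Equal school sizes are assumed, and R² is taken to shrink both variance components in proportion.

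**Step 1. Detectable effect.** d = (1.960 + 0.842) × SE = 2.802 × SE, with VIF = 1 + (m − 1) × ICC as in the article. The article does not say whether ρ applies to the school effect or to the whole school mean, so both readings are shown.

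(a) Model as written, no pair: SE² = (4/N)(1 − R²) × VIF
- Best: 0.04 × 0.5 × 1 = 0.020; SE = 0.141; d = 0.40
- Worst: 0.05 × 0.8 × 1.7 = 0.068; SE = 0.261; d = 0.73

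(b) Pair in the model, ρ on the school effect: SE² = (4/N)(1 − R²)[(1 − ICC) + m × ICC × (1 − ρ)]
- Best: 0.020; d = 0.40
- Worst: 0.04 × (0.9 + 0.4) = 0.052; SE = 0.228; d = 0.64

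(c) Pair in the model, ρ on all variance: SE² = (4/N)(1 − R²) × VIF × (1 − ρ)
- Best: 0.020 × 0.3 = 0.006; SE = 0.077; d = 0.22
- Worst: 0.068 × 0.5 = 0.034; SE = 0.184; d = 0.52

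| Version | Normal approximation | t-based |
|---|---|---|
| (a) no pair | 0.40–0.73 | 0.45–0.84 (8 df) |
| (b) pair, ρ on school effect | 0.40–0.64 | 0.53–0.86 (4 df) |
| (c) pair, ρ on all variance | 0.22–0.52 | 0.29–0.69 (4 df) |
| Stated in the article | 0.11–0.29 | |

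None of these standard versions reproduces 0.11 to 0.29. The closest, (c) with the normal approximation, gives about twice the stated values. Two non-standard formulas, each squaring (1 − R²), do round to the stated range, but this looks like coincidence.

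**Step 2. Power of the model as written at the top of the stated range, d = 0.29.**
- Best: Φ(0.29/0.141 − 1.96) = 54%
- Worst: Φ(0.29/0.261 − 1.96) = 20%

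**Step 3. What omitting pair does to the time-two standard error.** With ρ on the school effect, the ratio of the SE reported without pair to the true SE is √{[1 + (m − 1)ICC] / [(1 − ICC) + m × ICC × (1 − ρ)]}.
- ICC 0.05, ρ 0.5, m = 8: √(1.35/1.15) = 1.08
- ICC 0.10, ρ 0.7, m = 10: √(1.90/1.20) = 1.26
- ICC 0: ratio 1.00

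Simulation of five pairs of school means (200,000 replicates per setting) gives a two-sided type I error of about 0.02 to 0.04 without pair at ICC 0.05 to 0.10, and 0.05 with pair. At ICC 0 both are 0.05.

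**Step 4. What adding pair does to power.** Same simulation, d = 0.8 in residual-SD units:

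| Setting | No pair, 8 df | Pair, 4 df |
|---|---|---|
| m = 8, ICC 0 | 0.88 | 0.76 |
| m = 8, ICC 0.05, ρ 0.5 | 0.78 | 0.71 |
| m = 8, ICC 0.10, ρ 0.5 | 0.69 | 0.66 |
| m = 10, ICC 0.10, ρ 0.7 | 0.75 | 0.78 |

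Of these four settings, pairing wins only in the one with both ICC and ρ at the top of their ranges.

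**The case against.** **A condensed article may simply leave pair unmentioned.** The model description does not say that pairs will be ignored, the power section speaks of other baseline covariates, and an analysis plan that is not shown could include pair. So one cannot conclude that the matching will in fact be lost. But the article names the procedure, the clustering unit and the model terms, and the other covariates appear under the assumption about explained variance, separately from ρ. The mismatch between the two stated parts remains.

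**Leaving pair out does not invalidate the comparison.** A reader might infer that the standard error is simply wrong, or that false positives are a risk. Under the article's own assumptions the test is conservative, and at ICC = 0 it is exact on school means. Anti-conservatism would need teacher-level degrees of freedom together with matching that fails. The article states no df method, so that reading has no support in it.

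**A much larger loss is tempting but does not fit.** If ρ of 0.5 to 0.7 applied to observed school means, the SE would be inflated by 1/√(1 − ρ), or 1.41 to 1.83 times. If paired schools are linked only through between-school variance, the correlation of observed means cannot exceed m × ICC/[1 + (m − 1)ICC]. At ICC 0.10 that is 0.8/1.7 = 0.47 for m = 8 and 1.0/1.9 = 0.53 for m = 10. Most of that range lies beyond what the stated ICC allows.

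**Adding pair is not clearly better.** Step 4 bears this out, and it is why the fix offers two routes. Matching still serves the balance purpose given under Design even if the analysis is unpaired.

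**Conclusion.** The point holds as an inconsistency between the power calculation and the analysis. The range d = 0.11 to 0.29 relies on ρ, and the stated time-two model has no term through which ρ could act. For the model as written the inputs give about 0.40 to 0.73, or 0.45 to 0.84 with 8 df, and power at d = 0.29 is between 20% and 54%.

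The missing pair term is only part of the explanation, because full credit for ρ still gives 0.22 to 0.52. The stated range appears too small for ten schools on any standard reading.

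The effect on inference is modest: an SE about 8 to 26% too large and a type I error of about 0.02 to 0.04 if ρ acts on the school effect and ICC is 0.05 to 0.10, and none at ICC = 0. The maintenance analysis uses intervention schools only, one from each pair, and is unaffected.

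These figures assume equal school sizes and normal outcomes.

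**What to change.** Make the analysis and the power calculation describe the same test, by one of two routes:

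1. Add pair to the time-two model, either fixed or random with school nested in pair. Test the intervention effect with school-level small-sample df, and keep ρ in the power calculation, saying whether it refers to the school effect or the school mean.
2. Keep the unpaired model, give the reason, and remove ρ from the power calculation.

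In both cases recompute and restate the detectable effect for the chosen model, showing the formula and df, and revisit the statement that power is sufficient. Trial status says the data were not yet cleaned or finalised, so the choice can still be fixed before evaluation.

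The cost in work is at most one model term, one df specification and one recalculation. The restated detectable effect will be larger than the published one. Route 1 also cuts the df from 8 to 4, which lowers power over much of the assumed ICC and ρ range even when the matching works. With the school variance bounded at zero in REML, a pair term with 4 df does not by itself give exact size either: in simulation the type I error was about 0.005 to 0.014 with pair (4 df), against 0.014 to 0.021 without (8 df).

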### Implementation aims and hypotheses

***Firstly, we aim to evaluate the implementation fidelity of Professional Development*****(*****ParentCorps FUNdamentals and Coaching*****) for Ugandan teachers when implemented by Ugandan mental health professionals.** We hypothesize that Ugandan mental health professionals will implement Professional Development with high levels of fidelity.

**Secondly, within the context of an RCT, we aim to evaluate the impact of Professional Development on teacher practices in the classroom during the training school year, and during the following school year with different students.** We hypothesize that, relative to teachers in schools randomized to the waitlist control condition, teachers in intervention schools will use more effective practices in the classroom and these practices will be maintained over time and with a different student population.

**Thirdly, within intervention schools only, we aim to examine the relation between implementation fidelity, context (individual and system factors) and teacher practices.** We hypothesize that higher levels of implementation fidelity will be associated with greater use of effective practices in the classroom, and that positive school and teacher characteristics (such as better school leadership, and higher teacher self-efficacy) will predict higher teacher engagement in Professional Development and greater use of effective practices in the classroom overtime.

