### Participants

The study aims to enroll primary school and all early childhood teachers, including nursery pre-kindergarten and kindergarten, and primary one, two and three (first to third grades), serving students between four and eight-years-old. Based on our prior work, Ugandan primary schools have, on average, about 700 students (ranging from 100 to 2,300, SD = 440), 23 teachers (ranging from 7 to 56, SD = 13) and 54 students in each class (ranging from 15 to 90, SD = 21). The schools have on average six to eight early childhood teachers (for four to eight-year-olds). We anticipate that 80 to 100 early childhood teachers from the 10 study schools (40 to 50 teachers in each condition) will participate in the RCT, and estimate that more than 3,200 children across conditions (including waitlist control schools at the end of the trial) will be impacted during the study period ([name] and [name], unpublished observations). Although the trial is carried out in schools, parents, guardians and students are not considered subjects of this study. They will not participate in any research activity, therefore, consent of parents and guardians will not be obtained.

The study is being conducted by investigators from the United States and Uganda. All study recruitment and assessment procedures will be conducted by Ugandan research staff. Principals will be informed about the randomization procedures, study timeline, teacher assessments and intervention procedures (including immediate provision in the intervention schools and delayed provision in the control schools). Once principals agree to participate and sign a written agreement, teachers from the schools will be approached by research staff to assess their interest. Teachers will provide written informed consent and will be informed that they have the right to refuse to participate in the study, even though the principals and other teachers agree (with no negative consequences).

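### The rule for declaring maintained impact does not require that an impact was shown at time two, so it cannot tell a lasting effect from no effect

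*Protocol article*

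**What the plan says.** Analyses for aim two describes two models.

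- **Impact.** Time-two teacher practices are modelled "as a function of intervention, adjusting for time one teacher practices". This is the randomized comparison of intervention with waitlist schools.
- **Maintenance.** The second model drops the comparison group: "However, only the intervention sample will be analyzed (given that the waitlist control teachers will have received the intervention by time three"). Its data are the two post-intervention assessments: "We will use repeated data over time (times two and three"). Its form is: "We will model teacher practices post-intervention as a linear function of time, adjusting for baseline practices". The section then fixes how the result is read: "If the time effect is not significant, this will indicate maintenance of impact".

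No sentence makes the second conclusion depend on the result of the first model. The hypothesis that both models serve, in Implementation aims and hypotheses, has two linked parts. Relative to waitlist, "teachers in intervention schools will use more effective practices in the classroom and these practices will be maintained over time".

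**The concern.** The label refers to an impact, but the quantity tested is only stability. Teachers whose practices never improved will tend to be flat between times two and three, and the rule reports that flatness as maintained impact. Stable harm would be reported in the same way. A positive maintenance conclusion can therefore be returned when the first part of the hypothesis has failed.

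What is at stake is the follow-up conclusion, which is half of the aim-two hypothesis. If several practice measures or composites are analysed and only some show a time-two effect, the sentence as written would also attach maintained impact to those that showed none.

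**Working it through.** **The plan's own figure.** No error rate or power is given for the maintenance rule, so there is none to reproduce. The only power figure is the detectable d of 0.11 to 0.29 for the time-two comparison. A standard two-arm formula with the stated inputs gives about 0.22 to 0.52 instead. That discrepancy does not bear on this point, which depends only on the significance level.

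**Inputs from the protocol article**
- Teachers: "40 to 50 teachers in each condition", that is, five schools with 8 to 10 teachers each (Participants; Sample size and power).
- ICC: 0 to 0.10 (Sample size and power). The value 0.10 is used below.
- Level: the power section works "at 80% power of a 2-sided test with level of significance α = 0.05". No level is given for the time effect, so 0.05 two-sided is assumed.

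**Assumption not in the document**
- Within-school correlation of a teacher's repeated scores: 0.3 to 0.7.

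**Step 1: what the time coefficient measures.** Let δ₂ and δ₃ be the training effect at times two and three, and τ any other change between them (season, new class, secular trend). Among intervention teachers the expected change is

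(δ₃ − δ₂) + τ.

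Baseline is the same for a teacher at both times. With complete data, adjusting for it does not bring the gain over baseline into this coefficient. If δ₂ = δ₃ = δ, the effect cancels and only τ remains, whatever δ is.

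**Step 2: rate with τ = 0.** P(declare maintained) = 1 − α = 1 − 0.05 = 0.95 for every constant δ. Simulation with 20,000 trials per setting agrees:

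| True situation | Declared maintained |
|---|---|
| No effect, teacher-level test | 0.948 to 0.951 |
| No effect, school-level test (4 df) | 0.949 to 0.952 |
| No effect, and time-two test showed no favourable impact | 0.949 to 0.952 |
| d = 0.29 fully kept | 0.949 |
| Stable harm, d = −0.5 | 0.948 |

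**Step 3: no effect, but τ not zero.** Take 45 teachers, ICC 0.10 and correlation 0.5. The occasion variance is (1 − 0.5)(1 − 0.10) = 0.45, the change variance is 2 × 0.45 = 0.90, and the standard error of the mean change is √(0.90/45) = 0.141 SD. A shift of 0.2 SD is then 0.2/0.141 = 1.41 standard errors, which is missed in roughly 70% of trials. Simulated rates:

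| Shift between times two and three | Teacher-level test | School-level test |
|---|---|---|
| 0.1 SD | 0.90 | 0.92 |
| 0.2 SD | 0.72 | 0.80 |
| 0.3 SD | 0.45 | 0.63 |

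Unmodelled school-by-time variance of 0.02 to 0.10 lowers the teacher-level figure to between 0.93 and 0.86 and leaves the school-level figure at about 0.95.

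**Step 4: rate with a gate.** If a significant favourable time-two contrast is required first, the false declaration rate under no effect is 0.025 × 0.95 = 0.024 when the two tests are treated as independent. Simulated values run from 0.021 to 0.026 across the settings tried with no shift between times two and three.

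**The case against.** The strongest reply is that the sentence should not be read alone. The section takes the between-arm model first and maintenance second, the word impact presupposes that there is one, and the hypothesis is stated in the same order. The time-two result will be reported from the same teachers in any case, so a null there would sit beside the maintenance result. A formal gate is also the kind of detail that an article may leave to an analysis plan.

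Part of this stands. It lowers the practical risk, and the investigators may well intend the gate. But the article does not leave the rule open: it states a complete one, and followed as written that rule returns maintained impact for a flat null.

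It is also fair to say that the 95% is simply 1 − α. It needs the assumed 0.05 level and no other change between times two and three. Time three falls in a new school year with different students, so no change is a strong condition, and Step 3 shows how far the rate can drop.

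Three stronger readings are tempting, and the document does not support them.
- A reader might infer that an ineffective programme would be declared maintained 95% of the time whatever else happens. That holds only under the two conditions just named.
- A reader might infer that the rule is usually wrong when a small real effect exists but is not significant at time two. If that effect persists, the declaration is correct. Such cases show low time-two power, not a false rule.
- A reader might infer that the rule will be run on every measure separately. Preliminary analyses plans composites to limit the number of analyses, and no outcome-by-outcome rule is written.

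**Conclusion.** The concern holds as a badly fixed decision rule. The maintenance conclusion depends only on the change from time two to time three among intervention teachers. With a 0.05 two-sided test and no other change in that interval, it is positive in about 95% of trials when the training does nothing, the same rate as when a real effect is fully kept. With other change of 0.1 to 0.3 SD, the rate under no effect falls to between 0.90 and 0.45 (teacher level) or 0.92 and 0.63 (school level). The rule still cannot separate a lasting effect from none, because any constant effect cancels out of the coefficient.

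The randomized time-two conclusion is unaffected. The importance is moderate: the wording suggests that an impact is presupposed, but the rule does not require one.

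Reading a non-significant time effect as no loss is a separate weakness of the same sentence. In the simulation of Step 3, an effect of d = 0.29 that is entirely lost by time three is still called maintained in about 48% (teacher level) to 66% (school level) of trials. An equivalence margin on the change would address that weakness but not this one, since an ineffective programme measured precisely enough would meet the margin.

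**What to change.** Replace the sentence with an ordered rule. A claim of maintained impact is considered only for an outcome or composite whose time-two intervention-versus-waitlist contrast is significant in favour of intervention. For any other outcome, the change from time two to time three is reported descriptively with its confidence interval, and no maintenance claim is made.

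This takes one or two sentences and needs no new data or models. Trial status describes the data as not yet finalized for evaluation, so at that stage the change could still precede the analysis.

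The cost is that no maintenance claim is possible when a real time-two effect is missed. In the simulation, with an unpaired test on school means, a true d of 0.29 was significant at time two in about 25% of trials and a d of 0.5 in about 59%. An analysis that uses the matched pairs would give different figures.

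The gate alone does not make non-significance into evidence of no loss. That part of the sentence needs its own repair.

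### Maintenance is to be concluded from a non-significant time effect in the intervention arm alone, a rule under which a loss of about 0.2 SD would more often than not be called maintained

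*Protocol article*

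**What the plan says.** Under Implementation aims and hypotheses, the second aim of the protocol article includes the hypothesis that "these practices will be maintained over time and with a different student population".

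The test is described under Analyses for aim two. Because the waitlist teachers will have been trained by time three, "only the intervention sample will be analyzed". Practice at times two and three is modelled as a linear function of time, adjusted for baseline. On the variance structure the article says: "In addition to random intercepts and slopes for individual teachers, the model will include random effects for schools". The decision rule follows: "If the time effect is not significant, this will indicate maintenance of impact".

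The Participants section expects 40 to 50 teachers per condition, and five schools are allocated to intervention. The same section also says "The schools have on average six to eight early childhood teachers", which for five schools gives 5 × 6 = 30 to 5 × 8 = 40 teachers. The Sample size and power section covers only the two-arm post-intervention comparison.

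**The concern.** The hypothesis is that practice is maintained, and the rule confirms it whenever a test fails to reject no change. Anything that widens the standard error, such as fewer teachers or noisier ratings, makes the favourable verdict easier to reach. This is a rule the article states outright, so it is not a detail left to a fuller plan.

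At stake is the part of aim two that concerns the following school year. A false verdict of maintenance would feed the article's case for wider dissemination of the programme.

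**Working it through.** **The plan's own figure.** There is none for this test. The detectable range of d = 0.11 to 0.29 under Sample size and power is for the two-arm comparison at time two, and nothing below rests on it.

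**Inputs from the article.** n = 40 to 50 teachers in five schools, so m = 8 to 10 per school. Design effect VIF = 1 + (m − 1) × ICC. Two-sided α = 0.05, stated for post-intervention outcomes and applied here to the time effect. Earlier US teacher effects of 0.42 to 0.85, given under The mental health intervention.

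**Assumptions, not in the article.** Correlation r between times two and three of 0.5 to 0.7. ICC of the change of 0 or 0.05; the article's 0 to 0.10 is for teachers within schools in its power calculation.

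**Formula.** With two time points and complete data, the time effect is the mean within-teacher change, and a baseline main effect cancels from it. In SD units, SE = √(2(1 − r) × VIF / n). The chance that a loss δ is non-significant comes from the noncentral t distribution with noncentrality δ/SE. Two degrees-of-freedom choices bracket the analysis: n − 1 (teachers) and 4 (five schools minus one).

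**Numbers for δ = 0.21 (half of 0.42).**
- n = 40, r = 0.5, ICC 0: SE = √(1.0/40) = 0.158; 0.21/0.158 = 1.33; missed 75%.
- n = 50, r = 0.7, ICC 0: SE = √(0.6/50) = 0.110; 0.21/0.110 = 1.9; missed 53%.
- n = 50, r = 0.7, ICC 0.05, 4 df: VIF = 1 + 9 × 0.05 = 1.45; SE = 0.110 × √1.45 = 0.132; 0.21/0.132 = 1.6; missed 77%.

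**Chance that a true loss is non-significant, and so called maintained (n 40-50, r 0.5-0.7):**

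| True loss (SD) | Teacher df, ICC 0 | 4 df, ICC of change 0.05 |
|---|---|---|
| 0.20-0.21 | 53-77% | 77-86% |
| 0.25 | 39-66% | 69-82% |
| 0.32 | 18-49% | 54-73% |
| 0.42 | 4-26% | 33-58% |
| 0.64 | 0-2% | 6-26% |

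**Wider sensitivity range.** With r 0.3-0.7, ICC 0-0.10 and both df choices, a loss of 0.21 SD is missed 53-90% of the time, 0.42 SD 4-74%, and 0.64 SD 0-49%.

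**The same point without a power argument.** At teacher level with ICC 0, the 95% CI half-width runs from 0.22 SD (n = 50, r = 0.7) to 0.32 SD (n = 40, r = 0.5). An observed change of exactly zero would therefore leave a loss of 0.21 SD inside the interval, yet the rule would declare maintenance.

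**The case against.** A reader might infer that any real loss would usually be reported as maintained, or that half or more of the effect could vanish and generally go unseen. The article's figures do not support either reading. Half of the highest cited effect is 0.85/2 = 0.425 SD. At teacher level with ICC 0, a loss of about that size (0.42 SD, which is also complete loss of the smallest cited effect) would be missed only 4-26% of the time. A loss of 0.64 SD would be detected in most cases on either choice of degrees of freedom. The size of the loss has to be named.

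It is also fair that every probability rests on a correlation and an ICC of change that the article does not supply. The article takes steps against noise: two masked observers rate independently, measures must show adequate reliability, and similar measures are combined. It reports nothing on teacher turnover, so no claim is made about that. The between-arm comparison at time two is untouched by this sentence.

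These points limit the size of the problem but do not rescue the rule. No margin or interval criterion appears elsewhere in the article, and at about 0.2 SD the miss rate exceeds one half in every scenario tried.

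**Conclusion.** The concern holds for losses of stated size. A non-significant change between times two and three, in 40 to 50 teachers from five schools, cannot by itself show maintenance. Assuming r = 0.5 to 0.7, a true loss of about 0.2 SD would be called maintained about 53-77% of the time with teacher-level degrees of freedom. With 4 degrees of freedom and an ICC of change of 0.05 the figure is about 77-86%. For 0.25 to 0.42 SD the answer turns on the assumptions. Losses of 0.64 SD or more would mostly be detected.

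A separate limit applies however precise the estimate is. With no untreated group at time three, a flat course cannot be attributed to the intervention, because calendar or new-class effects could mask or mimic a change. The data can support a statement about stable practice in intervention teachers, but not about a maintained between-arm impact.

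**What to change.** Replace the decision sentence under Analyses for aim two with:

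*The change from time two to time three will be reported with its 95% CI. Maintenance will be concluded only if the limit on the side of loss excludes a fixed margin, set before the data are analysed and not derived from this trial's own time-two effect. Otherwise maintenance is inconclusive. A non-significant time effect alone will not be read as maintenance.*

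Word any favourable conclusion as stable practice in intervention teachers. A margin defined as a share of the observed time-two effect should be avoided: it is estimated with error, is not pre-set, and shrinks towards zero if that effect is small.

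**Cost.** The change needs wording and one margin, and no new data. The Trial status section says the data were not yet cleaned or finalized, so at the time of writing the rule could still be set ahead of the results.

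The real price is candour about precision. With a margin as tight as 0.21 SD and no true loss, the confidence limit would exclude the margin only about 25-47% of the time at teacher level (ICC 0), and 14-23% with 4 df and ICC of change 0.05. Inconclusive is then the most likely result even if nothing is lost. For 80% power at that margin, n = 2(1 − r) × VIF × ((1.96 + 0.84)/0.21)², which gives about 107 (r = 0.7) to 178 (r = 0.5) teachers with VIF = 1. A wider margin is easier to meet, but it must be defended as a tolerable loss; 0.42 SD would tolerate losing the whole of the smallest cited effect.
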